#### Qualitative analysis

Qualitative data will be assessed using thematic analysis. Thematic analysis consists of five stages: familiarisation, generating codes, constructing themes, revising themes, and defining themes [43]. Draft codebooks for each participant group (e.g. mentor mothers, adolescents, and friends/family members) will be developed on an initial sub-set of transcripts by two researchers in each site. Following refinement based on researcher consensus, the final codebooks will be used to code each transcript independently by two researchers in each site. Sub-categories will be assessed for the number of occurrences across all transcripts and themes and categories relevant to the data identified. Findings will be triangulated with quantitative data on implementation, and mentor mother and adolescent outcomes to assess the feasibility and impact of the intervention.

### Feasibility criteria for progression to full trial

The primary objective of this study is to evaluate the feasibility and acceptability of the intervention, its implementation, and trial procedures for a subsequent large-scale evaluation. Overall feasibility and acceptability criteria for progression to a full trial have been informed by Mellor et al.’s [44] trial progression recommendations and retention criteria used in previous mental health research conducted in LMICs [45]. These consist of a mixture of qualitative and quantitative criteria:Identification of qualitative themes reporting that both adolescents and mentor mothers perceive the intervention and mentor training as being acceptable, feasible, and appropriate.Retention of at least 67% (i.e. 33% loss to follow-up) of adolescents and mentor mothers through endline assessments.Fewer than 15% missing items on outcome measures across all assessments.Presence of adverse events among fewer than 10% of participants.Identification of serious adverse events related to intervention delivery.

In domains where criteria are met, we will retain the procedure for the full trial. In domains where criteria are not met, we will modify procedures for the full trial guided by data collected during interviews. The presence of any adverse events and/or serious adverse events will be addressed by the research team to identify alternative strategies for the full trial and Data Safety Monitoring Committee. The number of feasibility, acceptability, and fidelity criteria that are not met will determine the extent of intervention and trial design modification.

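### The progression criterion on serious adverse events is worded in the opposite direction to the other four and conflicts with the sentence on handling such events

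*Protocol article*

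**What the plan says.** All the relevant text is in the protocol article, under the heading Feasibility criteria for progression to full trial. The list is introduced with "Overall feasibility and acceptability criteria for progression to a full trial have been informed by" published recommendations and earlier research, so each item is presented as a progression criterion.

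The first item asks for qualitative themes showing that adolescents and mentor mothers find the intervention and the training acceptable, feasible and appropriate. The next three are "Retention of at least 67% (i.e. 33% loss to follow-up) of adolescents and mentor mothers through endline assessments", "Fewer than 15% missing items on outcome measures across all assessments" and "Presence of adverse events among fewer than 10% of participants". The fifth is "Identification of serious adverse events related to intervention delivery".

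Two action sentences follow: "In domains where criteria are met, we will retain the procedure for the full trial" and "In domains where criteria are not met, we will modify procedures for the full trial guided by data collected during interviews". A separate sentence then deals with harms: "The presence of any adverse events and/or serious adverse events will be addressed by the research team to identify alternative strategies", and goes on to mention the full trial and the Data Safety Monitoring Committee. The section closes by saying that the number of unmet feasibility, acceptability and fidelity criteria sets the extent of modification.

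**The concern.** A progression criterion works only if it is clear which result satisfies it. In four of the five items, the satisfying result is the one the investigators hope for. In the fifth, it is the detection of serious harm related to delivery. Since the section ties retention to met criteria and modification to unmet ones, the wording points the action the wrong way for this item.

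The pilot exists to decide which procedures go forward to a full trial, and its participants are pregnant girls aged 15–19, some of them minors. This is the only listed progression criterion specific to serious adverse events. A prespecified criterion should not need reinterpretation once the safety data are known, because its meaning is then settled by people who have seen the result.

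**Working it through.** No arithmetic applies, because the criterion carries no number. The check is to apply the section's met/not-met rule to each item in turn and compare directions.

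| Criterion | Result that meets it | Is that result favourable? |
|---|---|---|
| Qualitative themes | Themes reporting acceptability, feasibility and appropriateness are identified | Yes |
| Retention | At least 67% | Yes |
| Missing items | Fewer than 15% | Yes |
| Adverse events | Fewer than 10% of participants | Yes |
| Serious adverse events | Related events are identified | No |

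Four of five run one way and one runs the other. The first and fifth items open with the same noun, identification. In the first, identifying the themes is plainly what satisfies the criterion, so the list's own usage supports reading the fifth the same way.

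Next, set the two instructions side by side for the two possible results.

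- **One or more related serious adverse events.** The criterion is met, so the retain/modify rule says to retain. The harms sentence says to look for alternative strategies. These conflict.
- **No related serious adverse event.** The criterion is not met, so the retain/modify rule says to modify. The harms sentence is triggered only by the presence of events, so it does not correct this branch.

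Finally, the count of unmet criteria. The closing sentence names feasibility, acceptability and fidelity criteria, and does not name safety. The introduction, however, labels the whole list as feasibility and acceptability criteria. Whether the fifth item is counted is therefore open.

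- If it is counted, the other four are met and no related event occurs, the count as written is 1, where the evident intention gives 0.
- If it is counted, the other four are met and related events exceed whatever tolerance the sponsor intends, the count as written is 0, where the intention gives 1.
- If it is not counted, the count is unaffected, and only the retain/modify problem remains.

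No other part of the article states this criterion differently.

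**The case against.** The strongest reply is that the intention is obvious and the section already supplies the action. The harms sentence covers any adverse or serious adverse event and directs the team towards alternatives, which amounts to modification. It is also the more specific instruction. The neighbouring adverse-event item shows the intended direction, and no sensible team would treat an absence of related serious events as a failure. The item affects no randomisation, outcome or estimate in the pilot. The count governs only the extent of modification and is not a numerical gate.

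Most of this stands. It makes a drafting error by far the likeliest explanation, and it limits what can be claimed. A reader might infer that the plan would carry forward a procedure linked to serious harm, or that the decision is reversed in every case. The documents do not support that: the harms sentence points the other way, so the result is a conflict of instructions. Nor is the fifth item the only provision on serious harm, because the harms sentence names such events and the adverse-event item does not exclude them. Nor is a miscount certain, given the wording of the closing sentence.

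The reply does not repair the criterion. The harms sentence does not say which result counts as met, and because it applies to any adverse event it gives no pass/fail rule for related serious ones. It could also be argued that the fifth item means only that such events will be tracked. In that case it is not a criterion and cannot be scored, although the section lists it as one and attaches actions to its status. Condensation in a journal article is no answer either, because the criterion is stated here, in the wrong direction.

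**Conclusion.** The criterion is wrong as written. One of five progression criteria, the only listed one specific to serious adverse events, is satisfied by the unfavourable result. Combined with the retain/modify rule, it contradicts the harms sentence in the same section. It could also be scored the wrong way in the count of unmet criteria, if it belongs in that count.

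The conclusion assumes that each listed item is meant to be judged met or not met, as the action sentences imply, and that no wording elsewhere governs. It does not assume that the investigators would act on the literal text; they probably would not. The fault lies in a prespecified decision rule that must be reinterpreted before it can be used. It has no bearing on the pilot's estimates or analyses.

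A reader might go further and conclude that the criterion should be zero related events, should extend to study procedures, or should require committee review before any progression decision. The documents state none of these. They would be new safety rules, and they are for the sponsor to decide.

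**What to change.** 1. Restate the fifth criterion so that the favourable safety result is what meets it. Any tolerance for related serious adverse events is for the sponsor to set and write in.
2. Reconcile the restated criterion with the retain/modify rule and with the sentence on addressing adverse and serious adverse events, so that a related serious event leads to one stated action.
3. State whether this criterion enters the count of unmet criteria that sets the extent of modification.

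The cost is essentially one line of text, with matching clarification of the adjoining sentences. No data collection, sample size or analysis changes.

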### Identification of study limitation to inform a future trial

We will additionally monitor any issues related to recruitment, retention, assessments, and programme delivery throughout the study to identify and develop new strategies to improve our overall effectiveness and implementation science methodology. Local project co-ordinators will maintain constant dialog with the research team members who collect data, mentor mothers, and adolescent girls throughout the study. Information relevant to the conduct of the study will be shared with the project PI (TS) and Scientific Co-ordinator (KL).

## Discussion

Adolescent perinatal mental health has significant implications on the health of adolescents and their babies. However, few interventions have targeted the priorities, strengths, and needs for adolescent perinatal mental health in sub-Saharan Africa, where a large proportion of early pregnancies occur. The Thriving Mamas programme was co-designed with adolescent girls, their families, and communities to address this gap. Our understanding of the feasibility, acceptability, and appropriateness of the intervention beyond the perceptions of those involved in its development will allow for further refinement to its content and implementation strategies in preparation for testing its clinical impact. Additionally, the research will contribute to growing literature on the impact of co-design on the sustainability and success of mental health interventions.

Data collection is projected to begin in October 2023 and end in May 2024. As of September 2023, no participants have been recruited.

## Data Availability

Not applicable.

## Abbreviations

AIM: Acceptability of Intervention Measure
ENACT: Enhancing Assessment of Common Therapeutic Factors
FIM: Feasibility of Intervention Measure
GAD-7: Generalised Anxiety Disorder
IAM: Intervention Appropriateness Measure
INSPIRE: Innovative approaches to adolescent perinatal wellbeing
LMICs: Low- and middle-income countries
MICE: Multiple imputation using chained equations
MIDs: Clinical minimally important differences
MSPSS: Multidimensional Scale of Perceived Social Support
PHQ-9: Patient Health Questionnaire
SDS: Social Distance Scale
STAaRI: Standards for Reporting Implementation Studies
WHOQOL-BREF: World Health Organization Quality of Life brief version
